## Abstract

**Background:**

Optic neuritis is a frequent manifestation of multiple sclerosis. Visual deficits range from a minor impairment of visual functions through to complete loss of vision. Although many patients recover almost completely, roughly 35% of patients remain visually impaired for years, and therapeutic options for those patients hardly exist. Vision restoration therapy is a software-based visual training program that has been shown to improve visual deficits after pre- and postchiasmatic injury. The aim of this pilot study is to evaluate whether residual visual deficits after past or recent optic neuritis can be reduced by means of vision restoration therapy.

**Methods/design:**

A randomized, controlled, patient- and observer-blinded clinical pilot study (VISION study) was designed to evaluate the efficacy of vision restoration therapy in optic neuritis patients. Eighty patients with a residual visual deficit after optic neuritis (visual acuity ≤0.7 and/or scotoma) will be stratified according to the time of optic neuritis onset (manifestation more than 12 months ago (40 patients, fixed deficit) versus manifestation 2 to 6 months ago (40 patients, recent optic neuritis)), and randomized into vision restoration therapy arm or saccadic training arm (control intervention). Patients will be instructed to complete a computer-based visual training for approximately 30 minutes each day for a period of 6 months. Patients and evaluators remain blinded to the treatment allocation throughout the study. All endpoints will be analyzed and *P*-values < 0.05 will be considered statistically significant. The primary outcome parameter will be the expansion of the visual field after 3 and 6 months of treatment as determined by static visual field perimetry and high resolution perimetry. Secondary outcome variables will include visual acuity at both low and high contrast, glare contrast sensitivity, visually evoked potentials, optical coherence tomography and other functional tests of the visual system, alertness, health-related quality of life, fatigue, and depression.

**Discussion:**

If vision restoration therapy is shown to improve visual function after optic neuritis, this method might be a first therapeutic option for patients with incomplete recovery from optic neuritis.

**Trial registration:**

NCT01274702

## Background

Multiple sclerosis (MS) is one of the most frequent chronic diseases of the central nervous system (CNS) in young adults in western countries. The underlying pathomechanism is considered to be an autoimmune mediated attack against CNS structures that leads to CNS demyelination and neuroaxonal degeneration, and ultimately results in CNS dysfunction [1]. The course of the disease is typically relapsing-remitting in the beginning, followed by a secondary chronically progressive phase that is characterized by the accumulation of persistent neurological deficits. The therapeutic options comprise high-dose glucocorticosteroids in the acute phase and long-term immunomodulation or -suppression depending on the course and the dynamics [2]. An optic neuritis (ON) is the first symptom in 20 to 30% of MS patients, and approximately 50% of MS patients develop an ON at some point [3-6]. Leading symptoms of ON are reduced visual acuity, periocular pain (especially during eye movements), reduced contrast sensitivity, dysfunction of color vision, and visual field defects. In the majority of cases the loss of vision develops subacutely over a few days, whereas the recovery of the visual functions usually takes some weeks [3]. Although many patients recover almost completely, roughly 35% of patients remain visually impaired even after 10 years of onset [7,8]. Importantly, incomplete recovery of vision often leads to a reduced quality of life [9], and therapeutic options for those patients hardly exist [10].

Previous studies suggest beneficial effects of neuroplastic approaches for the treatment of visual deficits of neurological etiology [8,9]. Based on experiments with repetitive measurements of incremental thresholds at the edges of absolute visual field defects, Kasten and colleagues developed a software-based training program which is referred to as “vision restoration therapy” (VRT) [11]. The program (NovaVision AG, Magdeburg, Germany) can be run on a standard personal computer, which makes it suitable for home-based training. In a randomized, placebo-controlled, double-blind study on patients with pre- and postchiasmatic injury, VRT treatment expanded the mean visual field in the postchiasmatic group by 4.9° (± 1.7) whereas the mean visual field of the placebo group was reduced by 0.9° (± 0.8). The subgroup of patients with optic nerve injuries showed a trend towards a visual field expansion of 5.8° (± 1.2) in the VRT group compared to 4.3° (± 0.7) in the placebo group [11]. In patients with anterior ischemic optic neuropathy (AION), VRT resulted in a significant improvement of binocular reading speed and revealed positive trends on improvement of visual acuity, foveal sensitivity, and high-resolution perimetry (HRP). Moreover, all patients reported a subjective improvement of their visual function [12]. VRT is based on the hypothesis that visual units which are excluded from visual processing can be reintegrated by specific visual stimulation. Because of the diffuse nature of optic nerve lesions it is assumed that a smooth transition exists between severely and only moderately damaged retinal ganglion cells. Anope areas might, therefore, contain a number of capable but inhibited neurons. In fact, it has been demonstrated that even cortical blind patients have a residual visual sensitivity [13], and peripheral visual stimulation induced neural activity of central retinal ganglion cells in eyes with age-related macular degeneration [14]. It therefore appears likely that VRT stimulates residual retinal ganglion cells in visually impaired post-ON patients, and thus improves visual function [15-21].

Against this background, we introduce the protocol for a randomized, controlled clinical pilot study evaluating the efficacy of VRT in patients with incomplete visual recovery upon ON. We hypothesize that VRT is superior to saccadic training which is used here as a control intervention, with respect to i) restitution of residual visual field defects; ii) additional parameters of both visual function and integrity of the visual system including low contrast and color vision, conductivity, and retinal morphology; and iii) improvement in quality of life estimates.

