### Outcome parameters

The primary outcome parameter is the extend of the visual field after 3 and 6 months of training as determined by both HRP (see above) and threshold 30 degree automated perimetry (HFA 720, Zeiss Meditec AG, Germany). The secondary outcome parameters are outlined below and will be evaluated as displayed in Table 1. Visual acuity measurements are made using the Freiburg Visual Acuity and Contrast Test (FRACT): Landolt rings (ISO 8596) with a constant high contrast and decreasing size are presented at 4 m distance on a computer screen, and the patient is asked to report the perceived direction of the opening of each Landolt ring presented [26]. Contrast sensitivity is measured using FRACT with Landolt rings of equal size but decreasing contrast. Measurements of glare contrast sensitivity are made using the FRACT program as described above and a purpose built glare source (Beuth University of Applied Sciences, Berlin, Germany). The glare source consists of a white frame with eight white LEDs (approximately 8,500 LUX each) circularly arranged around the TFT-screen used for FRACT testing. Recording of VEP allows the conductance velocity and the amplitude of the visual signal evoked by stimulating the retina to be measured. In ON, both a delay of latency and lowered amplitude of this signal is typical. Spectral domain optical coherence tomography (OCT; Spectralis, Heidelberg Engineering, Germany; software version 5.1) is used to measure the retinal nerve fiber layer thickness (RNFLT) of the retina circularly around the optic nerve head and the volume of the macula, as both parameters are increasingly recognized as markers for neuroaxonal degeneration in MS [27]. Color perception is tested using pseudo-iso-chromatic plates (Ishihara, 14-plate version) and a Multi Color Anomaloscope (HMC, Oculus GmbH, Wetzlar, Germany), whereby the Ishihara test serves as a screening-test which is followed by an anomaloscope measurement in case of any abnormality [28]. The quality of stereoscopic vision is assessed using the stereo fly test (Titmus test). The patient wears polarized glasses and views a polarized fly. In normal stereoscopic vision a three-dimensional image of the fly is perceived. The cover/uncover test is performed to detect any strabismus or heterophoria. The International Reading Speed Texts (IReST) are used to measure the reading ability [29]. The Trail Making Test (TMT) is a popular neuropsychological test that provides information on visual search, scanning, speed of processing, mental flexibility, and executive functions. The patient is asked to connect 25 randomly spread numbers on a sheet of paper, and the time required for this task is measured [30]. The Tests of Attentional Performance (TAP 1.7) measure alertness via reaction time and provide a global measure of processing speed of the brain [31]. Alertness is defined as a state of general wakefulness in which a person can quickly react to concrete requirements. The questionnaires that are used to evaluate the health-related quality of life (HRQL) with regard to vision are the National Eye Institute Visual Functioning Questionnaire (NEI-VFQ 39) [32], the Impact of Visual Impairment Scale (IVIS) (which is the visual subscale of the Multiple Sclerosis Questionnaire of Life Inventory (MSQLI)) and a Visual Analogue Scale (VAS). The Short Form 36 (SF-36) is a generic measurement of the HRQL [33,34], the Health 49 is a freely available questionnaire (http://www.hamburger-module.de) [35] and the Fatigue Severity Scale (FSS) is a self-rating, nine-item questionnaire which measures the severity of fatigue [36] which has been validated in a large sample of MS patients [37]. The Beck Depression Inventory (BDI) is used mainly to control for depression as a possible confounder [38]. Finally, the following demographic data will be collected: disease course (clinically isolated syndrome or relapsing-remitting MS or secondary-progressive MS [39], date of first manifestation, date of first diagnosis, side of ON, current treatment, expanded disability status scale [40]), and vital parameters (blood pressure, heart rate, weight, body height, age, and ethnicity).

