
**Table 1 T1:** Visits and measurements

**Measurements**	**Visit 0 (baseline visit)**	**Visit 1 (after 3 months)**	**Visit 2 (after 6 months)**
Neurostatus	X		
Visual field	X	X	X
Contrast sensitivity	X	X	X
Glare sensitivity	X	X	X
Visual acuity	X	X	X
Visual evoked potentials	X	X	X
Optical coherence tomography	X	X	X
Color perception	X	X	X
Binocular vision	X	X	X
Eye movement/	X	X	X
Leading eye reading speed	X	X	X
Trial making test	X	X	X
Alertness	X	X	X
Health related quality of life	X	X	X

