### Statistical analysis

This study is designed as a pilot study because sufficient data that would allow a reasonable *a priori* calculation of sample size are not yet available. All endpoints will be analyzed and described descriptively. The null hypothesis is as follows: VRT has no influence on the visual outcome after ON. Evaluation of endpoints will be carried out by both “intention-to-treat” and “per-protocol” analyses. Statistical tests and presentations will be appropriate to the category and distribution of the respective variables. All tests will be accomplished with a type one error (α = 0.05; bilateral). All calculations will be performed using SPSS, Version 20 (SPSS, Inc., Chicago, IL, USA).

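### The protocol calls all endpoints descriptive, yet it states superiority hypotheses for open-ended secondary sets and declares any endpoint with P < 0.05 statistically significant, with no multiplicity control

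*Protocol article*

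**What the plan says.** Three parts of the article bear on the status of the secondary outcomes.

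- **Background, final paragraph.** VRT is hypothesised to be superior to saccadic training on three fronts. The first is the visual field (hypothesis i). The second is named as "additional parameters of both visual function and integrity of the visual system including low contrast and color vision, conductivity, and retinal morphology" (hypothesis ii). The third, hypothesis iii, is "improvement in quality of life estimates". All three hang on the same superiority statement. Set ii is open-ended, and no measure is designated for ii or iii.
- **Abstract, Methods/design.** "All endpoints will be analyzed and *P*-values < 0.05 will be considered statistically significant". The rule is not limited to the primary outcome.
- **Statistical analysis.** The study is a pilot without a sample size calculation, and "All endpoints will be analyzed and described descriptively". The same paragraph then states a null hypothesis and says "All tests will be accomplished with a type one error (α = 0.05; bilateral").

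On the number of measures, Outcome parameters says "The secondary outcome parameters are outlined below and will be evaluated as displayed in Table 1", and Table 1 schedules every listed measurement except the neurostatus at baseline, 3 months and 6 months. One instrument is set apart: "The Beck Depression Inventory (BDI) is used mainly to control for depression as a possible confounder".

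**The concern.** A reader cannot tell what a secondary result with P < 0.05 would be. Under the descriptive wording it is a summary of the data. Under the Abstract's rule it is a statistically significant finding, and under the Background it bears on a stated superiority hypothesis.

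The choice affects what the trial may report. If the visual field shows no difference, the written rule still allows a significant effect on glare sensitivity, or on one of several questionnaires, to be reported beside it. The Discussion says the trial is meant to corroborate the hypothesis ahead of larger confirmatory trials, so such a result could feed that decision. The stated 5% would not tell the reader how often it arises by chance across the whole secondary set.

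**Working it through.** **No figure to reproduce.** The article states no family-wise error rate. It gives only the per-test level, two-sided 0.05.

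**Number of measures (Outcome parameters).** Taking one score per instrument, but two each for VEP and OCT because the text names two quantities, gives 18: acuity, contrast sensitivity, glare contrast sensitivity, VEP latency, VEP amplitude, retinal nerve fibre layer thickness, macular volume, colour perception, stereopsis, reading speed, Trail Making Test, alertness (TAP), NEI-VFQ, IVIS, VAS, SF-36, Health 49 and FSS. The Beck inventory is left out as mainly a confounder control, and so is the cover test.

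Some of these are not clearly within hypotheses ii or iii. The Trail Making Test, alertness and fatigue are not named there, and the article does not say what Health 49 measures. Without these four, 14 remain.

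**Number of tests.** Two post-baseline visits give 18 × 2 = 36 or 14 × 2 = 28. A separate test at each visit is my assumption. Table 1 is a measurement schedule, not a list of tests.

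**Independent tests, VRT without effect on anything.**
- Either direction: 1 − 0.95^36 = 0.84; 1 − 0.95^28 = 0.76.
- Favouring VRT only (upper tail 0.025 per test): 1 − 0.975^36 = 0.60.
- Expected number of false positives, whatever the correlation: 36 × 0.05 = 1.8; 28 × 0.05 = 1.4.

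**Correlated tests.** The article gives no correlations, so a common correlation ρ between all test statistics is assumed and varied. With c = 1.96, φ and Φ the standard normal density and distribution function, and k tests, the two-sided probability is

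1 − ∫ [Φ((c − √ρ·z)/√(1−ρ)) − Φ((−c − √ρ·z)/√(1−ρ))]^k φ(z) dz.

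The favourable-tail version drops the second Φ term.

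| Tests | Counted | ρ = 0 | 0.3 | 0.5 | 0.8 |
|---|---|---|---|---|---|
| 36 | either direction | 0.84 | 0.72 | 0.55 | 0.27 |
| 28 | either direction | 0.76 | 0.64 | 0.49 | 0.25 |
| 18 (one visit) | either direction | 0.60 | 0.51 | 0.40 | 0.22 |
| 36 | favouring VRT | 0.60 | 0.38 | 0.28 | 0.14 |

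The nominal values are 0.05 for the first three rows and 0.025 for the last. The smallest entry in each row is still several times nominal: 0.22/0.05 = 4.4 for one visit, and 0.14/0.025 = 5.6 for results favouring VRT.

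**A structure closer to two visits.** A simulation of 18 outcomes at two visits, with separate correlations between outcomes and between visits (0.5 to 0.9), gives 0.51 to 0.61 in either direction and 0.26 to 0.32 favouring VRT at a between-outcome correlation of 0.5. At 0.7 the either-direction figure is 0.36 to 0.45.

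**The case against.** The strongest reply is that the exploratory framing is already there for the whole trial. The study is a pilot, endpoints are to be described, and the Discussion says that confirmation needs a larger study. The visual field is ranked as primary. Detailed multiplicity handling is commonly left to a full protocol or analysis plan, which is not shown. Most of this stands. It would be wrong to say that the article has no exploratory framing, and the lack of a ranking among secondaries would not be a finding by itself. What remains is text that the article does fix: a significance rule for all endpoints and superiority hypotheses for ii and iii. The pilot framing contradicts these but does not withdraw them.

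Two stronger readings are tempting, and the article supports neither.

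- A reader might infer that a chance-positive secondary is more likely than not. That depends on the unstated correlation, on testing at both visits and on counting both directions. With 36 tests it holds at ρ = 0.5 (0.55) but not at 0.8 (0.27); with one visit it already fails at 0.5 (0.40). For a false claim that VRT is superior, only the favourable tail counts, and that probability passes one half only near independence.
- A reader might infer that any single positive measure would establish hypothesis ii or iii. The article does not say so. It says only that such a result would be called statistically significant.

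**Conclusion.** The point holds as an internal conflict over the status of the secondary outcomes, with a measurable consequence. Descriptive reporting, superiority hypotheses and a blanket P < 0.05 rule cannot all govern the same outcomes. Over the range examined, the chance of at least one false positive is 0.27 to 0.84 for 36 tests and 0.25 to 0.76 for 28, or 0.14 to 0.60 for 36 tests when only results favouring VRT count. These figures rest on an assumed test at each visit, a count of measures that the article does not itself give, and an assumed common correlation. The precise size is therefore uncertain, but every figure examined is well above the stated level.

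This is a cheap improvement to what the trial may claim. It does not threaten the trial's validity, and the planned larger study limits the harm from a chance finding.

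**What to change.** 1. In the Abstract and in Statistical analysis, limit the P < 0.05 rule to the primary visual field outcome.
2. In Statistical analysis, state that the secondary outcomes under ii and iii are exploratory and are reported as between-arm differences with 95% confidence intervals, without a significance claim.
3. In the Background, reword ii and iii as exploratory objectives.

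I would not add a fixed-sequence test of selected secondaries after a positive primary. Outcome parameters defines the primary by two perimetry methods at two visits and does not say which combination counts as positive, so the gate could not be applied as the text stands.

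The cost is wording only: no extra patients, visits or measurements. The small downside is that an isolated secondary P < 0.05 can no longer be called statistically significant.

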## Methods/design

### Design and setting

The VISION study is a monocentric, randomized, controlled, and double-blind clinical trial conducted at the NeuroCure Clinical Research Center at the Charité - Universitaetsmedizin, Berlin, Germany. Recruitment started in 2011. Eighty patients with a diagnosis of past or recent ON will be stratified according to the onset of ON. The first group will comprise patients with ON manifestation at least 1 year in the past. The second group will comprise patients with ON onset between 2 and 6 months in the past. These two groups will be randomized 1:1 into the VRT group and the control intervention group, with the latter receiving a saccade training (RehaCom, Hasomed GmbH, Magdeburg, Germany). The detailed study design is provided below according to the revised CONSORT statement [22,23].

### Study cohort

Inclusion criteria for participation are: age between 18 and 55 years, ability to provide written informed consent, definite history of ON (supported by objective criteria-like visual evoked potentials (VEP) and/or typical clinical presentation), visual acuity between 0.05 (20/400) and 0.7 (~20/29) or >0.7 and scotoma (a basic visual function must be present to perform the training), and no systemic steroid treatment or plasmapheresis within the last 60 days. Exclusion criteria comprise occurrence of ON ≤ 60 days to avoid confounding by spontaneous resolving optic nerve edema, any other potentially confounding eye diseases (for example, macular degeneration, cataract, glaucoma, diabetic retinopathy), nystagmus, strabismus and amblyopia to avoid fixation errors and impaired binocular function, and a history of epileptic seizures because of repeated presentation of bright light stimuli.

### Randomization and blinding

A freeware program (http://www.random.org) is used to randomize subjects into VRT and control groups. Randomization is performed by an independent person otherwise not involved in the study. Access to the randomization lists is restricted to this person ensuring that the treatment allocation remains concealed to the recruiting and enrolling study personnel. Two members of the study team remain unblinded (KB, SW) in order to instruct and guide patients in all treatment-specific software issues. All information that could possibly reveal the study arm to both patients and blinded evaluators, such as the brand names or labels of the software or user manuals, are carefully avoided. All outcome parameters are determined in a blinded fashion. Patients asking for disclosure of treatment allocation will be put off until the end of the study.

### Ethics

The VISION study has been approved by the local ethics committee (Charité Campus Mitte; Berlin/Germany; no. EA1/078/10) and the Data Protection Department of the Charité and is registered at Clinicaltrials.gov (NCT01274702). The study will be conducted in accordance with the Declaration of Helsinki in its current version, the guidelines of the International Conference on Harmonization of Good Clinical Practice (ICH-GCP), and the applicable German laws. All participants are required to give informed written consent. No patient will be deprived of receiving a standard therapy.

### Treatment

#### Vision restoration therapy

VRT is a commercially distributed computer-based visual training program (NovaVison AG, Magdeburg, Germany). This software is based on the measurement of the visual field at baseline using HRP that detects the horizontal 43 degrees and vertical 32 degrees of the visual field like a common perimeter with supra-threshold stimuli and a higher resolution. The aim is to determine the border between a scotoma and normal areas of the visual field in a more precise way than standard automated perimetry does. The VRT software uses algorithms based on the HRP data to stimulate specifically receptive fields close to scotoma borders. VRT is performed using a chin support placed in front of the monitor at a distance according to the size of the monitor to ensure that the light beam of the stimuli reaches the correct areas of the retina. Patients are instructed to exercise for 30 minutes every day over a total period of 6 months. During each training session, 400 white light supra-threshold stimuli are presented on a computer-screen (duration 2000 ms each) and have to be confirmed by the patients by pressing a key within 1000 ms. Central fixation is important and is facilitated by a central color-changing dot (31 pixels) on which the patient continuously has to fixate and confirm each color change by pressing a key. For a maximum training effect, stimulus parameters such as the areas of stimulus presentation, stimulus size, duration and brightness undergo monthly adaptation to any change in the visual field.

